7.2.9 Atherosclerosis

7.3 END-POINT CLASSIFICATION 46

CHAPTER 8. DATA ANALYSIS 47

8.1 INTRODUCTION 47

8.2 PRETREATMENT CHARACTERISTICS 47

8.3 OUTCOME VARIABLES 48

8.3.1 Events.

8.3.2 Continuous variables.

8.4 CLINICAL COURSE AND PROGNOSIS 49

APPENDIX A. GLOSSARY 50

APPENDIX B. CENTERS AND INVESTIGATORS 51

APPENDIX C. REFERENCES 52

ABBREVIATIONS

Coronary Heart Disease

Cardiovascular Disease

IGT Impaired Glucose Tolerance

DPS Diabetes Prevention Study. Short version of Prevention of Diabetes in Persons with Impaired Glucose Tolerance: A Clinical Trial.

HbA1c Glycosylated hemoglobin, fraction A1c

HPLC High pressure liquid chromatography

NIH National Institutes of Health

OGTT Oral glucose tolerance test

WHO World Health Organization

Insulin-dependent diabetes

Non-insulin-dependent diabetes

CHAPTER 1. SUMMARY

A randomized clinical trial will be performed in middle-aged Finnish people to determine whether treatment of obese, sedentary adults with impaired glucose tolerance (IGT) will prevent or delay the development of type 2 diabetes.  The study will be conducted in several centers, will include 560 subjects, and will have a mean duration of 5.5 years per subject.  Subjects will be allocated at random to a standard or special diet-exercise treatment. Subjects will be enrolled over a two-year time period. Those enrolled during the first year will be treated for 6 years, and those enrolled during the second year will be treated for 5 years, so that all treatment cycles will finish during the final year of the study. The study is designed to have a power of 80% to detect a reduction of 30% or more in the incidence of diabetes by the diet-exercise program.

The applicant investigators have already demonstrated the feasibility of screening for IGT in their countries and providing effective interventions of the type to be used in this clinical trial. **This trial belongs to the category of "interventions in IGT and early diabetes in high-risk non-insulin-dependent diabetes mellitus populations on development of diabetes and its complications", which was recommended by the U.S. National Diabetes Advisory Board (1991) as a priority area for research in diabetes. No such studies have been initiated in this important issue so far, in spite of these unanimous recommendations by the world experts.**

CHAPTER 2. STUDY RATIONALE AND OBJECTIVES

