3.8 SAMPLE SIZE AND ENROLLMENT GOAL

We begin sample size determination by estimating the 5-year incidence of diabetes in the untreated persons with IGT to be 28% (see Chapter 2). Because of the uncertainty in the data needed to make this estimate, this figure may be an underestimate of the incidence of diabetes. If so, the power of the study would be greater than the following computations indicate. We are designing the study to be large enough to be able to detect, with 80% power (beta = 20%) at the 2-tailed 5% significance level (alpha = 5%), a 30% reduction in diabetes incidence due to diet-exercise treatment, ie, a reduction from 28% to 19.6%.

The possibility of a reduction in diabetes incidence by at least 30% is suggested by the results of the Malmöhus study (Sartor, et al, 1980) analyzed in accordance with randomized treatment assignment and by the nonrandomized treatment study of Eriksson and Lindgärde (1991). We are assuming that noncompliance in the DPS will be no worse than in these previous studies; therefore we are making no further adjustment for noncompliance. We will, however incorporate an adjustment for losses to follow-up, including deaths.

Letting p1 and p2 denote, respectively, the proportion of events (incidence of diabetes) in the control and treated groups, respectively, then, according to Halperin, et al (1968), the sample size required in each of the two groups is

N = {Zα[2p(1 - p)]1/2 + Zß[p1(1 - p1) + p2(1 - p2)]1/2}2 / [p1 -p2]2,

where p = (p1 + p2)/2 and Zα and Zß are the normal deviates associated with α and ß. With p1 = .28, p2 = .175, α (2-tailed) = .05, and ß = .20, the total minimum required sample size becomes

2N = 500.

In Malmöhus County from 1962-87, the mortality rate among persons aged 45-64 with IGT by WHO criteria was 19/1000 persons per year (Knowler, et al, in preparation), yielding an estimated 5.5-year cumulatie mortality rate of 10% in study participants. Allowing for 10% losses to follow-up from deaths over a 5.5-year period increases the sample size to

2N = 500/(1 - .10) = 556, or approximately 560.

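### The 560 subjects are sized for a 37.5% reduction in diabetes incidence; power for the 30% reduction the protocol claims is about 60%, not 80%

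*Protocol*

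**What the plan says.** Section 3.8 starts by "estimating the 5-year incidence of diabetes in the untreated persons with IGT to be 28" per cent. It then gives the effect to be detected with 80% power at the two-tailed 5% level: "a 30% reduction in diabetes incidence due to diet-exercise treatment, ie, a reduction from 28% to 19.6" per cent. Chapter 1 (Summary) makes the same promise: "The study is designed to have a power of 80% to detect a reduction of 30% or more in the incidence of diabetes".

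After printing the two-proportion formula for "the sample size required in each of the two groups is", Section 3.8 puts in the numbers: "With p1 = .28, p2 = .175". It obtains 2N = 500, divides by 0.90 and arrives at 556, rounded to 560.

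On losses, the section first says that it will adjust for losses to follow-up, deaths being one kind. The adjustment it makes reads: "Allowing for 10% losses to follow-up from deaths over a 5.5-year period increases the sample size to" 556. The 10% is taken from a mortality rate of 19 per 1000 per year. No adjustment is made for noncompliance.

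**The concern.** Section 3.8 uses two different treated-group incidences. The stated target is 19.6%; the value in the formula is 17.5%. If the sample size comes from 17.5%, the trial is sized for a larger effect than the one it says it can detect, and the 80% power claim in Section 3.8 and the Summary is wrong for this design.

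What is at stake is how a non-significant result would be read. On the protocol's wording, a true 30% reduction would be missed one time in five. If power is near 60%, it would be missed about two times in five, and a null result would say much less against a 30% effect than readers have been told.

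The loss allowance is a smaller matter of the same kind: an adjustment described as covering losses in general covers deaths only.

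**Working it through.** **Inputs (all from Section 3.8).** p1 = 0.28; stated p2 = 0.28 × 0.70 = 0.196; p2 entered = 0.175; two-sided α = 0.05 (z = 1.960); power 80% (z = 0.8416); equal groups; 10% inflation. The relative reduction implied by 0.175 is (0.28 − 0.175)/0.28 = 37.5%.

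**Formula as printed**, with p = (p1 + p2)/2:

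N = {zα√[2p(1 − p)] + zβ√[p1(1 − p1) + p2(1 − p2)]}² / (p1 − p2)²

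**Step 1: reproduce the protocol's figure with p2 = 0.175.**
p = 0.2275. N = (1.960 × 0.5929 + 0.8416 × 0.5882)² / 0.105² = (1.1620 + 0.4950)² / 0.011025 = 2.7457 / 0.011025 = 249.05.
Rounded up, this is 250 per group, so 2N = 500, and 500/0.90 = 556. The printed figures reproduce exactly.

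**Step 2: the same formula with the stated target, p2 = 0.196.**
p = 0.238. N = (1.960 × 0.6023 + 0.8416 × 0.5993)² / 0.084² = (1.1804 + 0.5044)² / 0.007056 = 2.8386 / 0.007056 = 402.3.
Rounded up, this is 403 per group, so 2N = 806, and 806/0.90 = 896. (Without rounding each group up: 805 and 894.)

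Variants for 28% versus 19.6% do not give 500 either: continuity-corrected 852, unpooled variance 799, arcsine 801, one-sided 634.

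**Step 3: power of the trial as sized.** Rearranging the formula:

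power = Φ{[|p1 − p2|√N − zα√(2p(1 − p))] / √[p1(1 − p1) + p2(1 − p2)]}

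For 0.28 versus 0.196 with 252 per group (560 less 10%): (0.084 × 15.875 − 1.1804)/0.5993 = (1.3335 − 1.1804)/0.5993 = 0.255, and Φ(0.255) = 0.601.

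| Evaluable per group | 30% reduction | 37.5% reduction |
|---|---|---|
| 250 (2N = 500) | 59.7% | 80.2% |
| 252 (560 less 10%) | 60.1% | 80.5% |
| 280 (no losses) | 64.6% | 84.4% |

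At 252 per group, the smallest reduction from 28% detectable with 80% power is about 37%.

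**Step 4: time-to-event check.** Assume constant hazards, 280 per group, 5.5 years each, and deaths censored at 0.019 per year.
- Control hazard: −ln(0.72)/5 = 0.0657.
- Treated hazard for 19.6%: −ln(0.804)/5 = 0.0436, so HR = 0.664.
- Expected events per group: 280 × λ/(λ + 0.019) × [1 − exp(−5.5(λ + 0.019))], totalling 137.7.
- Power: Φ(½√137.7 × |ln 0.664| − 1.960) = Φ(0.442) = 67%.

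On the same basis, 17.5% gives HR 0.586, 131.7 events and power of about 87%. The reduction in 5-year risk detectable with 80% power is about 35%.

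**Step 5: the loss allowance.** 1 − exp(−0.019 × 5.5) = 9.9%, so deaths alone use up the whole 10%. The protocol gives no figure for other losses. Taking total losses of 15% and 20% as assumptions:

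| Total loss (assumed) | Evaluable per group | 30% reduction | 37.5% reduction |
|---|---|---|---|
| 15% | 238 | 58% | 78% |
| 20% | 224 | 55% | 76% |

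**The case against.** The strongest reply is that 60% is the pessimistic end. Section 8.3.1 analyses events by the life-table method, in which subjects who die contribute follow-up until death, so removing 10% outright is conservative. Mean follow-up is 5.5 years, not 5. At a constant hazard the control incidence becomes 1 − 0.72^1.1 = 30.3%, and power for a 30% reduction is then about 64% at 250 per group and 69% if all 560 are evaluable. Section 3.8 warns that 28% may be too low, and 560 is described as a minimum. These points stand, and a range of 60% to just under 70% is fair. None restores 80%. With 250 evaluable per group, a 30% reduction would need a control incidence of about 39%, whereas the protocol's 28% already includes the 1.74 multiplier applied to 16% in Section 2.2.2. Noncompliance cannot explain 17.5% either: no adjustment is made, and one would move p2 towards p1, not away from it.

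On losses, the sentence that applies the 10% does attribute it to deaths. Section 2.3.2 (personal identification numbers, access to addresses and vital status) and the exclusions in Section 5.1.2 give reasons to expect few other losses. That makes this part minor: the promise is wider than the adjustment, and the 15% and 20% scenarios are illustrations, not forecasts.

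Finally, Section 8.1 commits to standard errors or confidence intervals, which would limit misreading of a null result. They would not correct the power claim.

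**Conclusion.** The concern holds. The 500, 556 and 560 belong to 28% versus 17.5%, and the claim of 80% power for a 30% reduction is contradicted by the protocol's own formula. On the protocol's method and loss allowance, power for the stated target is 60%. It is 65% with no losses and 67% by log-rank with constant hazards, 5.5 years of follow-up and deaths censored. The chance of missing a true 30% reduction is therefore about 40% (about one third by log-rank), against the stated 20%. Meeting the stated target would take about 896 subjects, some 336 more than planned. These figures rest on the 28% control incidence and equal groups. The conclusion that 80% is not reached also survives the more favourable assumptions considered above. The loss wording is a secondary defect and the main finding does not depend on it.

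**What to change.** Keep 560 and correct the wording in Section 3.8 and the Chapter 1 Summary so that target effect, p2, sample size and power agree:

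- State that 560 subjects (504 after 10% losses) give 80% power for a 37.5% reduction, from 28% to 17.5%.
- State that power for a 30% reduction, from 28% to 19.6%, is about 60% by the printed formula.
- If time-to-event figures are quoted, give them for both effects with their assumptions: about 67% for 30% and 87% for 37.5%.
- Describe the 10% consistently as an allowance for deaths only, and show power at assumed total losses of 15% and 20%.

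This costs protocol wording only and adds no subjects, but the sponsor must accept openly that the trial is underpowered for a 30% reduction. If 30% is to remain the effect detectable with 80% power, p2 = 0.196 has to go into the formula and the enrolment goal rises to about 896. The present text cannot stand with both the 30% claim and 560.

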3.9 PRETEST OF PROCEDURES AND DATA FORMS

During the 2-year screening period the DPS investigators will review the study design and detailed provisions of the Manual of Operations and agree on any revisions that seem appropriate. Data forms will be developed and the Policy and Safety Committee will meet for the purpose of reviewing and approving the Manual of Operations. The DPS investigators will then conduct a pretest of study procedures and data forms.

For the pretest, each Clinical Center will select 3 subjects who are found not to have IGT on screening. These subjects will undergo as many of the DPS study procedures as may be appropriate, eg, medical history, blood pressure, anthropometric, and laboratory measurements. Upon completion of the pretest, the procedures and data forms will be revised as appropriate.

CHAPTER 4. VISIT AND DATA SCHEDULE

4.1 OVERALL SCHEDULE

The schedule of examinations is summarized in Table 4.1. The starting date for enrolling subjects in the randomizized treatment period is designated as the beginning of year 1 of the study. Recruitment and enrollment should be completed by the end of year 2, i.e., two years later. All subjects will complete the study during the seventh year of the study. The closing date for each subject enrolled during the first year of the study will be the 6th anniversary of his/her randomization. The closing date for each subject enrolled in the second year will be the 5th anniversary of his/her randomization. Thus each subject will have either 5 or 6 years of follow-up, and follow-up of all subjects will be completed during one year.

4.2 SCHEDULED VISITS

Complete descriptions of the examinations at the visits are given in Chapter 5 and of the treatments in Chapter 6. Subjects will participate in the following visits (see Table 4.1):

4.2.1 Screening Visits. The screening OGTTs, eligibility measurements and medical history are performed at these 2 visits.

4.2.2 Enrollment Visit.

At this visit there is a physical examination by a physician for determination of eligibility. If the subject is eligible, clinical and biochemical measurements and randomization take place. The subject is counseled on the standard or special diet-exercise according to the random assignment.

4.2.3 Interim Visits. These visits occur at about 1-month intervals after enrollment for 3 months and at 3-month intervals for the remainder of the five or six years of follow-up. The visits occurring at annual intervals after enrollment are designated Annual Visits. Subjects receive diet-exercise counseling at interim visits according to the random assignment.

4.2.4 Annual Visits. At each of the five or six Annual Visits all biochemical tests, including the OGTT, are performed, the clinical measurements are made, and subjects receive diet-exercise counseling according to the random assignment.

4.3 TIME WINDOWS

For each visit, a time window is specified (Table 4.1). If the visit fails to occur within the time window, then it is a missed visit.

Table 4.1 FLOW SHEET FOR DATA COLLECTION

Clinical

Months & bio- Diet &

from History & chemical Diet & Exerc. Time window

enroll- Name Exam by measure- Exercise counsel- (y = years)

ment of visit OGTT Physician ments1 History ing2 and   (d = days)

monitoring

-2 1st Screening +

-1 2nd Screening + + +

0 Enrollment + + +

1 Interim + 16- 45 d

2 Interim + 46- 75 d

3 Interim + + 76-106 d

6 Interim + + 167-227 d

9 Interim + + 289-319 d

12 Annual + + + + + 320-410 d

15 Interim + + 1 y + 46-136 d

18 Interim + + 1 y + 137-227 d

21 Interim + + 1 y + 228-318 d

24 Annual + + + + + 1 y + 319-410 d

27 Interim + + 2 y + 46-136 d

30 Interim + + 2 y + 137-227 d

33 Interim + + 2 y + 228-318 d

36 Annual + + + + + 2 y + 319-410 d

39-60 or -723

End of treatment+34 + +

End of treatment+6 + +

1 See Chapter 5.

2 For subjects assigned to intensive diet-exercise, additional group sessions will occur, and for some subjects additional visits with dietary and exercise personnel will be required, especially during the first year. For subjects assigned to the standard diet-exercise program, counseling will be given only at the enrollment visit.

3 Months 39-60 (for those followed 5 years) or 36-72 (for those followed 6 years) will be the same as months 27 through 36 except for the yearly increments of the time windows.

4 See Section 5.5.

CHAPTER 5. ELIGIBILITY, SCREENING, AND EXAMINATION PROCEDURES

5.1 ELIGIBILITY AND EXCLUSION CRITERIA. To be eligible for

participation in the DPS, subjects must meet the following eligibility

criteria.

5.1.1 Eligibility criteria

o **Impaired glucose tolerance defined as follows**:

**a**) the mean of 2-hour plasma glucose of two OGTTs >7.8 and <11.0. If the mean is <7.8, and the 2-hour value of the first OGTT is >7.8 and the 2-hour value of the second OGTT is <7.8 and the fasting plasma glucose of the second OGTT is >5.5, then a third OGTT is performed and the mean 2-hour glucose is counted for the first and third OGTT

**OR**

**b**) one OGTT with fasting plasma glucose 6.4-7.7 and 2-hour value 7.8- 11.0

**OR**

**c**) random plasma glucose value after at least 4 hour fast 6.4-7.7 (or capillary blood -> 5.6-6.4) and one OGTT with 2-hour value 7.8-11.0.

o **Obesity, defined by body mass index >25 kg/m2**

o **Age 40-64 years**

o Willingness, after receiving a thorough explanation of

the study, to participate. Subject indicates willingness by signing the consent form.

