3.2 SUBJECT ELIGIBILITY AND EXCLUSION CRITERIA

3.2.1 Definitions of diabetes and IGT. The classification of and diagnostic criteria for diabetes and other categories of glucose tolerance will be based on criteria adopted by the World Health Organization (WHO), (World Health Organization, 1985). According to WHO criteria, the diagnosis of diabetes may be established on the basis of:

1) casual plasma glucose concentrations  11.1 mM (200 mg/dl) on one occasion with symptoms or on two without,

2) fasting venous plasma glucose concentrations  7.8 mM (140 mg/dl) on more than one occasion, or

3) oral glucose tolerance tests meeting the criteria shown in Table 3.1. IGT is diagnosed when the criteria for diabetes are not met, but the 2 hour post‑load plasma glucose is from 7.8 to 11.0 mM (140 to 199 mg/dl).

TABLE 3.1. DIAGNOSTIC VALUES FOR THE ORAL GLUCOSE TOLERANCE TEST

ACCORDING THE WORLD HEALTH ORGANIZATION (WHO)

Venous plasma glucose concentration

mM mg/dl

IGT Fasting < 7.8 <140

and 2 hour 7.8‑11.0 140‑199

Diabetes Fasting > 7.8 >140

or 2 hour >11.1 >200

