5.1.2 Exclusion criteria

o Previous diagnosis of diabetes other than gestational diabetes (diabetes first diagnosed during a pregnancy) which has not persisted after pregnancy

o Previous treatment for IGT other than with routine dietary and health advice (persons previously given intensive diet or exercise treatment for IGT or other metabolic conditions such as hyperlipidemia will be excluded)

o Participation in a regular program of vigorous physical exercise

o A myocardial infarction or a by-pass operation less then 1 year ago o Hypersensitivity to diet or exercise program

o Chronic illness that makes 6-year survival improbable, or illness which requires or is likely to require treatment known to affect glucose tolerance (e.g. corticosteroid drugs)

o Mental or medical characteristics that are likely to interfere with informed consent, compliance with diet, exercise, or long-term follow-up

These eligibility and exclusion criteria are specified for the following reasons. The age range of 40-64 years is chosen to include a target population old enough for IGT to have a substantial prevalence to make screening feasible and young enough that the mortality rate will not cause many censored observations when development of diabetes is the primary endpoint. Pregnancy is to be avoided because of its effects on glucose tolerance and interference with treatment procedures. Subjects must be overweight and not participating in a vigorous exercise program, because weight loss and exercise will be components of the diet-exercise intervention. As first occurrence of diabetes will be the primary endpoint, it must not already have been diagnosed at entry. Previous treatment of IGT (such as by diet or exercise) may have established permanent changes in behavior which would make randomization to the standard diet-exercise group impractical. Entry of patients treated with drugs known to affect glucose tolerance would confuse interpretation of findings. The other medical contraindications are to avoid randomizing patients who would be unlikely to be able to maintain randomized treatment throughout the study.

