5.2 SCREENING FOR IGT

5.2.1 Population selected for screening. Cases of IGT to be studied will be found by population screening. The type of population screened will vary from one Clinical Center to another; some will select a sample representative of the general population while others will select subjects thought to be at high risk of IGT (eg, subjects who are obese, have hypertension, or have relatives with type 2 diabetes).

5.2.2 Conditions for the screening examination. Prior to the screening examination, any acute intercurrent illness or injury must be resolved and treatment of any chronic condition (such as hypertension, arthritis or hyperlipidemia) must be stabilized so that the test is performed under stable conditions.

5.2.3 The oral glucose tolerance test.

The OGTT should be administered in the morning after at least three days of unrestricted diet and usual physical activity. The test should be preceded by an overnight fast of 10-16 hours, during which water may be drunk. Smoking is not permitted during the test. The presence of factors that influence interpretation of the results of the test must be recorded (e.g., medications, inactivity, infection, etc.). In the first screening OGTT blood glucose may be analysed from capillary whole blood with a Hemocue-analyser, which is fast, easy, cheap, and yet reliable method in blood glucose screening.

After collection of the fasting venous blood sample (or capillary blood sample in the first OGTT), the subject should drink 75 g of anhydrous glucose (or partial hydrolysates of starch of the equivalent carbohydrate content or 82.5 g glucose monohydrate) in 250-300 ml of water over the course of 5 minutes. Venous (or capillary) blood samples will be collected at 1 and 2 hours after the test load (only at 2 hours in the first screening OGTT).

The blood sample should be collected in a tube containing NaF and centrifuged within 15 minutes to separate the plasma; the plasma should be kept at 4oC up to 12 hours or frozen until the glucose concentration is measured. In addition, at fasting a blood sample will be collected in a tube containing EDTA for measurement of HbA1c by high pressure liquid chromatography (HPLC).

Subjects with previously known IGT can be tested by this proce­dure to determine if they still have IGT, but must be excluded if they have been actively treated for IGT (see Section 5.1.2).

The test will be interpreted and acted on as follows:

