1. Subjects with 2hr plasma glucose (or capillary whole blood glucose) <7.4 mM (<133 mg/dl) will be told that they have normal glucose tolerance, are ineligible for the study, and that no further action is indicated.

2. Subjects with 2hr plasma (or capillary whole blood) glucose 7.4‑11.3 mM (133-199 mg/dl) are asked to come to another OGTT after at least one week. Subjects with mean 2hr glucose 7.8-11.0 of two OGTTs are

diagnosed as having IGT and are further evaluated for eligibility to partic­ipate in the DPS.

3. Subjects with mean 2hr glucose >11.1 mM (>200 mg/dl) are diagnosed as having probable diabetes and are referred to the usual source of medical care for confirmation and treatment of diabetes.

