5.3 SCREENING EXAMINATIONS

5.3.1 Conditions for examination are discribed in section 5.2.2.

5.3.2 Content of first screening examination.

This examination will include an OGTT and the following measurements

(1) Height (to the nearest cm without shoes).

(2) Weight (to nearest 0.1 kg in light indoor clothes, without shoes).

5.3.3 Content of second screening examination.

This examination will include an OGTT. Previous diagnoses or treatment for diabetes, IGT, or gestational diabetes will be sought. If present then the patient is ineligible for inclusion in the trial (see 5.1.2). Treatment for hypertension, hyperlipidemia, other serious illnesses and use of medicines, alcohol and tobacco will be recorded. The following measurements are made

(3) Measurement of waist and hip circumferences.

(4) Measurement of sagittal and transverse diameters.

(5) 12-lead supine resting ECG (to be forwarded to the ECG Reading Center).

5.3.3 Content of enrollment examination. This examination will include a medical history and physical examination by a physician.

The following core data will be obtained and recorded:

(6) Blood pressure measured with a mercury sphygmomanometer (1st and 5th phase).

(7) Fasting venous blood specimens for serum total and HDL cholesterol, serum triglycerides, serum creatinine, liver function tests (serum bilirubin, alkaline phosphatase, albumin, and ALT or AST), thyroid stimulating hormone, HbA1c by HPLC, and an extra 10 ml of serum to save frozen.

(8) HLA-typing and storage of DNA samples for genetic markers.

(9) WHO cardiovascular questionnaire will be completed.

(10) Subjects will be asked to complete a dietary diary.

(11) Physical activity (occupational and leisure) will be assessed by questionnaire.

(12) Assessment of physical fitness by walking test.

(13) B-mode ultrasound imaging of carotic arteries.

(15) Lean body mass using Futrex infrared equipment.

(16) Hemostatic factors: The activity of the hemostatic system, and its contribution to the progression and complications of atherosclerosis will be assessed by measuring fibrinogen, F VII:C, prothrombin fragment F1+2 and PAI-1 activity both **in the beginning and at the end of the study**.

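### Eligibility route 5.1.1(a) and the 5.2.3 screening rules set no upper fasting-glucose limit, contradicting Table 3.1 and the endpoint definition; 5.3.3 also contradicts 5.1.2 on prior IGT and gestational diabetes

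*Protocol*

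**What the plan says.** **Entry criteria, 5.1.1.** There are three alternative routes.
- Route (a) requires "the mean of 2-hour plasma glucose of two OGTTs >7.8 and <11.0". Its only fasting figure is a lower bound that triggers another test: "the fasting plasma glucose of the second OGTT is >5.5, then a third OGTT is performed".
- Route (b) does cap the OGTT fasting value: "one OGTT with fasting plasma glucose 6.4-7.7 and 2-hour value 7.8- 11.0".
- Route (c) caps a separate glucose value, taken after at least four hours' fasting, at 7.7 mM. For the OGTT itself it requires only the 2-hour value.

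**Screening rules, 5.2.3.** Rule 2 takes forward "Subjects with mean 2hr glucose 7.8-11.0 of two OGTTs". Rule 3 refers subjects as probable diabetes on the mean 2-hour value alone. Neither rule uses fasting glucose.

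**General definition, 3.2.1 and Table 3.1.** The IGT row begins "IGT Fasting < 7.8 <140" and adds the 2-hour range of 7.8-11.0 mM. Fasting glucose above 7.8 mM (as printed) is enough on its own for diabetes.

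**Endpoint, 6.2.2 and 7.1.** Diabetes is fasting glucose above 7.8 mM or 2-hour glucose above 11.1 mM, confirmed by a repeat OGTT a week later. The first scheduled test is at month 12.

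**Prior diagnoses.** Section 5.3.3 states: "Previous diagnoses or treatment for diabetes, IGT, or gestational diabetes will be sought. If present then the patient is ineligible for inclusion in the trial", and cites 5.1.2. But 5.1.2 excludes "Previous diagnosis of diabetes other than gestational diabetes" that has not persisted after pregnancy; in other words, it exempts such women. It excludes previous IGT treatment only beyond routine advice. Section 5.2.3 adds: "Subjects with previously known IGT can be tested", with exclusion only after active treatment.

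**The concern.** The primary endpoint is the first occurrence of diabetes, and the rationale in 5.1.2 says it must not already have been diagnosed at entry. The entry rule should therefore exclude everyone who already meets the endpoint's glucose criteria. Route (a) checks one of the two glucose values and the endpoint accepts either. A subject can thus enter on an in-range 2-hour value while already over the line on fasting glucose.

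Such a subject is a prevalent case. If the fasting value persists, the subject is recorded as an incident event. To the extent that treatment cannot undo the event, it adds equally to both arms, pulls the risk ratio towards 1 and costs power.

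The 5.3.3 wording raises a different problem. A centre that follows 5.3.3 and one that follows 5.1.2 would reach different decisions on the same woman with past gestational diabetes, or on the same person with known but untreated IGT.

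**Working it through.** **1. Logic check.** Three illustrative pairs of screening OGTTs (fasting / 2-hour, mM) were put through route (a), the 5.2.3 recall range, Table 3.1 and the endpoint values in 7.1.

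| First OGTT | Second OGTT | Mean 2-hour | Passes 5.1.1(a) | Diabetic by Table 3.1 | Two diabetic OGTTs, as 7.1 requires |
|---|---|---|---|---|---|
| 8.0 / 9.0 | 8.2 / 9.4 | 9.2 | yes | both tests | yes |
| 6.0 / 11.3 | 6.0 / 10.5 | 10.9 | yes | first only | no |
| 6.0 / 7.4 | 6.0 / 14.5 | 10.95 | yes | second only | no |

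All three first tests fall in the 7.4-11.3 mM recall range of rule 2. The first row is the defect: an eligible subject whose screening values already satisfy the endpoint's values and its repeat-test rule. In the other rows averaging hides one diabetic 2-hour value, but the confirmed endpoint is not met.

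**2. The plan's own sample size (3.8).** Inputs: p1 = 0.28, p2 = 0.175, two-sided alpha 0.05, power 80%, using the formula in 3.8 with mean p = 0.2275. N = {1.96 × √[2(0.2275)(0.7725)] + 0.8416 × √[0.28(0.72) + 0.175(0.825)]}² / 0.105² ≈ 249-250 per arm, so 2N = 500, and 500/0.90 = 556. The plan's figures reproduce. Power at 250 per arm is 80.2%.

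**3. Dilution.** Let f be the share of randomised subjects who are prevalent cases by fasting glucose. The protocol gives no value, so f is assumed. Assume also that every such subject becomes an event in either arm. Each arm's rate is then f + (1 − f) × p.

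| f | Prevalent cases per 250 | Control | Treated | Risk ratio | Power |
|---|---|---|---|---|---|
| 0% | 0 | 0.2800 | 0.1750 | 0.625 | 80% |
| 1% | 2.5 | 0.2872 | 0.1833 | 0.638 | 78% |
| 3% | 7.5 | 0.3016 | 0.1998 | 0.662 | 75% |
| 5% | 12.5 | 0.3160 | 0.2163 | 0.684 | 71% |

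**4. Sensitivity to the second assumption.** Suppose treatment prevents confirmation in 30% of these subjects (illustrative). The treated rate is then 0.7f + (1 − f) × 0.175. For f = 1% this is 0.1803 against 0.2872, with power 81%. For f = 3% it is 0.1908 against 0.3016, with power 82%. The loss of power disappears.

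**5. Units in rule 2.** At 18.016 mg/dl per mM, 11.3 mM = 203.6 mg/dl and 199 mg/dl = 11.05 mM. The two upper ends of the recall range differ.

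**6. Prior diagnoses, side by side.**

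| History | 5.3.3 | 5.1.2 | 5.2.3 |
|---|---|---|---|
| Gestational diabetes, not persisting | ineligible | exempt from exclusion | not addressed |
| Known IGT, not actively treated | ineligible | not excluded | may be tested |

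The contradiction needs no assumption.

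**The case against.** The strongest reply is that the fasting ceiling is already in the protocol. Section 3.2.1 diagnoses IGT only when the diabetes criteria are not met, the glossary points to Table 3.1, and 3.2.2 says subjects will have IGT. This rules out the reading that the protocol has no fasting limit anywhere. It does not remove the defect. Section 3.2.2 sends the reader to 5.1 for the full criteria, 5.1.1 supplies its own definition of IGT, and route (b) states a fasting range where route (a) does not. A centre applying 5.1.1 and 5.2.3 as written would enrol the subject in the first row of the logic check.

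Second, a reader might infer that such a subject becomes an event at once and in either arm. The documents do not support that. The event counts only after the annual OGTT at month 12 and a confirmatory repeat, unless diabetes is suspected clinically sooner, and a normal or IGT repeat returns the subject to treatment. Section 2.3.1 reports normalised glucose tolerance in more than half of a lifestyle-treated group. Section 3.6 says normalisation is rare in type 2 diabetes, but it counts suppression below detection as treatment success. Irreversibility is therefore an assumption, and the sensitivity check shows that the direction of the power effect depends on it.

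Third, the 5.3.3 sentence itself points to 5.1.2, centres are meant to screen different populations, and randomisation is stratified by centre. A reader might infer a biased treatment comparison; the documents do not support that. What remains is inconsistent eligibility.

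**Conclusion.** The contradiction stands on the text. The entry rules in 5.1.1(a) and 5.2.3, and the OGTT part of route (c), omit a fasting condition that Table 3.1 makes part of IGT and that 6.2.2 and 7.1 make sufficient for the endpoint. Confirmed prevalent cases can be randomised.

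The size is modest and conditional. If 1-3% of subjects are affected and treatment cannot reverse them, power falls from 80% to about 78-75% and the risk ratio moves from 0.625 to 0.64-0.66. Neither condition comes from the protocol. A starting power of about 60% might be inferred from the 19.6% rate named in 3.8, but that reflects the separate mismatch between 19.6% and the 17.5% used in the formula and should not be charged to this point.

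The conflict between 5.3.3 and 5.1.2/5.2.3 is certain as text, and its effect on enrolment is unquantified. The unit mismatch is minor: it affects who is recalled for a second OGTT, not the final eligibility range. The documents do not show which of the two figures is the slip.

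**What to change.** 1. Reconcile 5.1.1(a) and (c) and rules 2-3 of 5.2.3 with Table 3.1 and 7.1, so that nobody who already meets the protocol's definition of diabetes at screening is randomised.
2. State how the fasting criterion applies when the first screening OGTT uses capillary whole blood, since Table 3.1 is in venous plasma. A plasma limit simply imposed on every OGTT would not fit those subjects.
3. State whether a fasting value must be repeated to exclude. Section 3.2.1 requires fasting values on more than one occasion, and 7.1 requires a repeat OGTT.
4. Replace the 5.3.3 sentence with a reference to 5.1.2, and reconcile 5.1.2 with 5.2.3 on known IGT.
5. Reconcile the mM and mg/dl limits in rule 2.

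The thresholds and exclusions are for the investigators to choose. The cost is wording: a fasting sample is already part of the screening OGTT, although the first may be capillary. The downside is that a few screened subjects become ineligible.
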